### 1.1.1 Background on PR006A

PR006A is an investigational gene therapy being developed as a disease-modifying, one-time treatment for FTD-GRN. PR006A utilizes an adeno-associated virus serotype 9 (AAV9) viral vector to deliver a functional copy of the wildtype *GRN* gene, which encodes the wildtype PGRN, to a patient's cells. PR006A contains elements to constitutively express *GRN* under the control of the cytomegalovirus enhancer (CMVe) and chicken  $\beta$ -actin (CBA) promoter using a codon-optimized coding sequence for human *GRN*. The vector shares most features of other AAV9 vectors that have been used safely in clinical studies, including clinical studies for spinal muscular atrophy type 1 (Mendell et al 2017).

The AAV9 vector is particularly well suited for gene therapy of CNS disorders given its ability to transduce multiple CNS cell types, the persistence of expression of the transgene, and its safety record (Samulski and Muzyczka 2014; Weinberg et al 2013). As multiple brain

regions are affected in FTD-GRN, broad biodistribution of PR006A is needed. Based on NHP research, broad brain distribution is best achieved by injecting investigational product (i.e., PR006A) into the cisterna magna ([Hinderer et al 2018](#); [Zerah et al 2015](#); [Gray et al 2013](#)). However, localized intracerebral adeno-associated virus (AAV)-GRN gene therapy has been reported to correct disease-related phenotypes in *Grn* knockout (KO) mice ([Arrant et al 2018](#)), demonstrating that it is possible to express active PGRN in the brain to restore function through cross-correction.

Finally, while the precise role of PGRN in healthy and diseased brains is only partially understood, the gene therapy approach does not rely on a detailed mechanistic understanding of PGRN function or the multiple biological pathways it affects. Instead, the rationale for this gene therapy approach relies on the well-established knowledge that patients who carry a single copy of a mutated *GRN* gene have substantially reduced levels of PGRN and a 90% likelihood of developing FTD. Replenishing PGRN levels both intra- and extra-cellularly in the brain by broadly delivering copies of the functional wildtype *GRN* gene is predicted to provide clinical benefit via all PGRN-related mechanisms relevant for the disease process.

### 1.1.2 Nonclinical Overview

PR006A efficacy was evaluated in 2 models of FTD-GRN: (1) an in vitro induced pluripotent stem cell (iPSC)-derived neuronal culture (iPSC-neuron) model, which uses cells from patients carrying heterozygous *GRN* mutations, and (2) an in vivo *Grn* KO genetic mouse model. These models were chosen as they recapitulate the underlying PGRN deficiency observed in patients with FTD-GRN. The iPSC-neuron model expresses approximately one-half of normal PGRN levels and has impaired lysosomal function. The *Grn* KO mice completely lack PGRN and exhibit lysosomal and neuroinflammatory phenotypes.

In vivo studies were conducted in the *Grn* KO mouse model, which is the most frequently used animal model in preclinical studies of FTD-GRN and which have a complete loss of PGRN expression. While the most accurate mouse genetic model approximation to patients with FTD-GRN vis-à-vis PGRN levels would be mice with a heterozygous loss-of-function *Grn* mutation, such mice fail to demonstrate a phenotype that is consistent with the human disease. In contrast, *Grn* KO mice display age-dependent phenotypes, including lysosomal alterations, neuronal lipofuscin accumulation, ubiquitin accumulation, microgliosis, and neuroinflammation, recapitulating many key pathological features of human FTD-GRN. Three nonclinical in vivo efficacy studies were performed: 2 single-dose studies in aged

*Grn* KO mice and a dose-ranging study in adult *Grn* KO mice. PR006A was administered via intracerebroventricular (ICV) injection, as ICM injection (the intended clinical route of administration) is technically difficult in mice. In-life safety assessments and post-mortem histopathology by a blinded board-certified pathologist were also performed in these experiments.

In the single-dose studies in 14- to 16-month-old aged *Grn* KO mice (PRV-2018-027, PRV-2019-002), PR006A was delivered by ICV injection at a dose of  $2.4 \times 10^{11}$  vg/g brain, and the animals were sacrificed 2 months post-injection. PR006A resulted in broad transgene biodistribution and PR006A-encoded PGRN expression throughout the CNS (i.e., cerebral cortex and spinal cord) and peripheral tissues. PR006A reduced key FTD-GRN-related phenotypes in the brain of *Grn* KO mice, including accumulation of lipofuscin and ubiquitin, markers indicative of lysosomal abnormalities, and proinflammatory cytokine expression and microgliosis, markers indicative of chronic CNS inflammation. Post-mortem histopathology on all major organs revealed no adverse PR006A-related findings.

In a dose-ranging study (PRV-2019-004), 4-month-old adult *Grn* KO mice were delivered PR006A by ICV injection at a low dose ( $2.7 \times 10^9$  vg/g brain), mid dose ( $2.7 \times 10^{10}$  vg/g brain), or high dose ( $2.7 \times 10^{11}$  vg/g brain), and the animals were sacrificed 3 months post-injection. PR006A effectively transduced *Grn* KO mice, resulting in a dose-dependent biodistribution of the transgene. PR006A treatment also led to production of progranulin mRNA and PGRN in the CNS. A dose-response relationship between PR006A and decreased lipofuscinosis was observed throughout multiple regions of the brain. A statistically significant reduction of lipofuscinosis was observed at the mid and high doses of PR006A. PR006A decreased ubiquitin accumulation throughout multiple brain regions at all doses. A reduction in gene expression of proinflammatory cytokine and microgliosis markers to wildtype levels was observed in the cerebral cortex at all doses of PR006A. In the brain, PR006A also decreased protein expression of microgliosis markers at all doses and astrogliosis markers at the high dose. Post-mortem histopathology on all major organs showed no adverse PR006A-related findings.

The in vitro human neuronal model of progranulin haploinsufficiency was used since it is an excellent tool to assess FTD-GRN-related phenotypes such as TDP-43 pathology that do not present in the in vivo *Grn* KO mouse model. iPSC lines from 2 independent heterozygous *GRN* mutation carrier patients and from a healthy-aged subject with no *GRN* mutation were

differentiated into neuronal cultures for efficacy experiments. The level of PGRN in FTD-GRN iPSC-derived cell lines was approximately 25% to 50% of control cells, consistent with replicating the effect of progranulin haploinsufficiency on plasma PGRN levels in FTD-GRN patients. PR006A effectively transduced human cells in vitro, resulting in a dose-dependent production of PGRN. PR006A ameliorated TDP-43 pathology in the FTD-GRN iPSC-neurons. In addition, PR006A reversed deficits in the maturation of the lysosomal enzyme cathepsin D, a necessary step for normal lysosomal function.

In addition to the mouse studies described above, safety and biodistribution of PR006A were evaluated in 2 toxicology studies using cynomolgus macaques. The brain of the NHP is most similar to that of humans, and the anatomical features of the NHP spinal cord and CSF volume and flow permits an ICM injection, thus mimicking the route of administration intended for clinical dosing. Because of the anatomical similarities to humans, it is expected that NHP studies will provide more reliable biodistribution data supporting clinical dosing of PR006A.

A pilot, non-GLP (Good Laboratory Practice) NHP study (PRV-2018-021) using PR006A research-grade material was conducted to confirm that PR006A is well tolerated following ICM administration. Animals were treated with either  $4.9 \times 10^{12}$  vg of PR006A ( $6.6 \times 10^{10}$  vg/g brain, assuming a brain weight of 74 g) or excipient alone. The study duration was 4 weeks post-injection, the anticipated peak expression time point. There were no unscheduled deaths, and all monkeys survived until the scheduled necropsy. No differences were noted in the functional observation battery, food consumption, or weight gain throughout the duration of the study between the control monkeys that received excipient and monkeys that were treated with PR006A.

Tissue samples were collected from the brain and peripheral organs for histopathology. Tissues were processed and stained with hematoxylin and eosin for evaluation. In animals injected with PR006A, meningeal and perivascular mononuclear inflammatory cell infiltrates were observed throughout the brain. This finding was consistently minimal in severity. The results were considered inconclusive, since this was a small (n=2/group) pilot study.

In the 6-month, multidose GLP NHP toxicology study (PRV-2018-028; n=6-7/dosing group), male and female cynomolgus monkeys 2 to 4 years of age were treated with PR006A administered once via ICM injection with a 7-day, 30-day, or 183-day post-administration

observation period. The study evaluated 2 dose levels: the highest dose ( $6.5 \times 10^{10}$  vg/g brain) was the maximum feasible dose achievable at the time of the experiment with 1.2 mL volume of undiluted test product, and the low dose ( $6.5 \times 10^9$  vg/g brain) is equivalent to one log lower than the high dose. The study also included a control arm in which animals received 1.2 mL of excipient only (20 mM Tris pH 8.0, 200 mM NaCl, 1 mM MgCl2, and 0.001% poloxamer 188). No adverse PR006A-related clinical observations, body weight changes, ophthalmic observations, or physical or neurological examination findings were noted. No in-life, clinical pathology, or anatomic pathology observations were observed that were considered related to PR006A.

No PR006A-related microscopic findings were observed in Day 7 or Day 30 animals. At the terminal sacrifice at Day 183, PR006A-related microscopic findings were observed in the dorsal funiculus of the cervical, thoracic, and (to a lesser extent) the lumbar spinal cord and the dorsal root ganglia (DRG).

Animals administered  $6.5 \times 10^9$  vg/g or  $6.5 \times 10^{10}$  vg/g had minimal axonal degeneration and, sometimes, minimal gliosis limited to the dorsal funiculus (white matter). Axonal degeneration was characterized by a few scattered nerve fibers ( $\leq 10$  per entire cross section) consisting of dilated axonal myelin sheaths that were either empty or containing cellular debris and/or phagocytic cells or spheroids (swollen eosinophilic axons). Gliosis was co-localized with axonal degeneration and was characterized by a few ( $\leq 10$ ) more fusiform nuclei (i.e., microglial cells) near affected axons. The limited extent of the degeneration in this study supported an interpretation that these changes were non-adverse.

Minimally increased cellularity, related to enhanced numbers of satellite glial cells, in small clusters occurred in the DRG of a few PR006A-treated animals at the terminal sacrifice. This change was noted in 1 male administered  $6.5 \times 10^9$  vg/g (Group 2) and 1 male and 1 female administered  $6.5 \times 10^{10}$  vg/g (Group 3). This finding was characterized by rare (1 to 2 per section), loosely packed aggregates of oval- to spindle-shaped cells located among DRG neurons. The finding was consistent with a glial reaction to a prior neuronal injury and is a known consequence of gene therapy investigational products (i.e., AAV vectors) designed for CNS targets.

An apparent increase in DRG autophagy was noted in investigational product-treated males, a common background finding in cynomolgus monkeys. This finding was considered not to

be PR006A-related because the number of animals at the terminal sacrifice was small and a few controls also had the finding; thus, ganglion autophagy was considered not PR006A-related.

At Days 7 and 30, minimal or slight mixed cell infiltrates and/or minimal hemorrhage in the brain (characterized by focal areas of meningeal perivascular accumulations of lymphocytes, macrophages, neutrophils, and erythrocytes) were observed in controls and PR006A-treated animals. In addition, at Day 183, PR006A-treated animals had increased injection site muscle degeneration or mononuclear infiltrates at injection sites. The findings were of minimal severity and the number of animals in the terminal sacrifice was small. Therefore, all of these findings were considered procedure related (intracisternal injection) and not related to PR006A.

Overall, there have been no adverse PR006A treatment-related findings observed in the mouse or NHP studies.

## **1.2 Study Rationale**

### **1.2.1 Overview**

The purpose of this Phase 1/2 open-label study is to assess the safety, tolerability, immunogenicity, and effects of PR006A on PGRN levels in plasma and/or CSF, as well as its immunogenicity and effects on biomarkers and efficacy parameters, in order to inform further clinical investigation and/or allow marketing registration of PR006A in a patient population suffering from FTD-GRN.

### **1.2.2 Rationale for Patient Population**

This study will enroll FTD-GRN patients at the symptomatic stage of the disease, based on results of a CDR plus NACC FTLD SB score of at least 1 and less than or equal to 15. Pathogenic *GRN* mutation carrier status will be confirmed during Screening; patients with all null mutations including nonsense, frameshift, splice site mutations, and complete or partial (exonic) *GRN* gene deletions will be considered for enrollment. Carriers of *GRN* missense mutations may be included provided a specific mutation has previously been demonstrated to be pathogenic.

Individuals harboring pathogenic *GRN* mutations have PGRN haploinsufficiency with an approximately 50% decrease of normal PGRN levels and are known to be at 90% risk to develop FTD by 75 years of age. Hence, the PR006A mechanism of action is relevant to patients with pathogenic *GRN* mutations. The Sponsor's clinical hypothesis is that treatment with PR006A will increase brain PGRN levels, modify the disease processes, and slow or halt clinical progression.

### 1.2.3 Rationale for Staggering of Patient Enrollment

Based on available nonclinical data, no specific safety signals are anticipated in humans, other than potential risk for liver enzyme elevations related to AAV9-capsid-specific T-cell responses observed in previous human studies with AAV9 vectors ([Mendell et al 2017](#)). In order to monitor for any unexpected safety events in humans, including but not limited to potential transitory liver enzyme elevations, in each cohort, enrollment will be staggered by at least 8 weeks between the first 2 patients and then at least 8 weeks between the second patient and the remaining 3 patients of the cohort to permit review of safety, tolerability, immunogenicity, and, to the extent available, efficacy by the iDMC, who will ultimately provide a recommendation on further dosing. This 8-week monitoring period was established to capture the reported time-frame for liver enzyme elevations caused by T-cell responses, which were observed at approximately 3 weeks post-dosing ([Mendell et al 2017](#)). It also ensures the iDMC will have appropriate biomarker and safety data from the Month 2 visit to make their recommendation. Since presumably, CSF inflammatory changes occur between 1 and 2.5 months post-dosing, at least 8 weeks after the second staggered patient is dosed in Cohort 1, the iDMC will review all available safety, tolerability, immunogenicity, and, to the extent feasible, efficacy results from the first 2 patients in this cohort (dosed in a staggered manner). At the recommendation of the iDMC, the Sponsor will decide whether to dose the remaining 3 patients in Cohort 1 (low dose) without staggering and in parallel begin staggered enrollment in the mid-dose cohort (Cohort 2).

Escalation to the mid-dose ( $7.0 \times 10^{13}$  vg) [REDACTED] level cohorts will be based on iDMC recommendation, assessments of safety and biomarker data from the clinical PR006A low- and mid-dose cohorts, as well as technical feasibility (e.g., the ability to obtain sufficient concentrations of PR006A within the limitations of injectate volume).

Once enrollment of at least 2 patients in the low-dose cohort is complete and at least 8 weeks have elapsed after the second patient is dosed, the iDMC will review cumulative tabulated

data from the low-dose cohort and recommend whether or not to initiate dosing in the mid-dose cohort. The mid- [REDACTED] dose cohorts will utilize the same approach (staggered patients followed by unstaggered patients) as the low-dose cohort. The same iDMC data review process will be followed once at least 2 patients have enrolled in the mid-dose cohort and at least 8 weeks have elapsed after the second patient is dosed, [REDACTED]  
[REDACTED]

The Sponsor will perform 3 formal interim analyses: 1) after all patients complete 12 months of treatment in Cohort 1; 2) after all patients complete 12 months of treatment in Cohort 2; [REDACTED]. Additionally, the Sponsor will perform a review of biomarker data at regular intervals. Based on the review of data through Month 2 in at least 2 patients and in consultation with the iDMC, a decision will be made to continue or suspend enrollment in any enrolling cohorts and to start enrollment in the subsequent cohort (i.e., dose escalate). A decision to dose escalate will be based on data from at least 2 patients from the concurrent cohort. However, all cohorts will enroll a minimum of 3 patients, unless enrollment is terminated due to safety concerns or based on biomarker review this dose is considered to be non-efficacious. In all other circumstances, the full cohort of 5 patients will be enrolled. Additional interim analyses may be performed during the follow-up period (post-Year 1) based on Sponsor's discretion.

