#### **5.5.1.3 Immunosuppression Monitoring Criteria**

In addition to monitoring sirolimus trough levels, the Investigator should evaluate patient's clinical status, lab findings and potential AEs.

Consideration should also be given to the need to increase doses of the immunosuppressant agent, prolong the tapering regimen, add a third agent or re-initiate treatment based on clinical signs or symptoms consistent with an immune response, including:

- Asymptomatic pleocytosis with WBC > 30 mm^3 and/or high CSF protein (> 70 mg/dL)

- CSF pleocytosis and/or increased protein accompanied by clinical symptoms (including decompensation of underlying FTD symptoms)
- Emergence of sensory symptoms based on neurological examination and/or TNAS.
- ALT and/or AST elevation  $>5 \times$  ULN in conjunction with hepatitis symptoms (e.g., jaundice, fatigue)
- ALT and/or AST elevation  $>10 \times$  ULN irrespective of the presence or absence of clinical symptomatology

The Investigator should consider implementing a longer prednisone taper over an additional 4 weeks in patients presenting with ALT and/or AST  $>3 \times$  ULN at the end of the initial 14-day taper. In case of AST/ALT elevations refractory to prednisone treatment, the Investigator should seek expert advice from a hepatologist.

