### 11.1 Monitoring

#### 11.1.1 Independent Data Monitoring Committee

An iDMC consisting of clinicians and a biostatistician otherwise unaffiliated with the conduct of the study will conduct a review of the safety, tolerability, and immunogenicity data; and, to the extent available, efficacy data in accordance with the charter. Members of the iDMC will not be allowed to participate as Investigators in this study and must not have competing interests that could affect their roles with respect to the study. The iDMC will assess safety variables as listed for the primary safety endpoints outlined in [Section 2](#). The iDMC may recommend protocol modification(s), including dose recommendations and study termination, based on their review of the nature, frequency, and/or severity of an AE(s) to ensure patient safety and the ethical continuation of the study. The study stopping rules are described in [Section 4.2.4](#).

Enrollment will be staggered for the initial 2 patients receiving the low dose ( $3.5 \times 10^{13}$  vg) of PR006A in Cohort 1, such that at least 8 weeks will separate dosing of each patient. This staggering will permit review of safety, tolerability, immunogenicity, and, to the extent available, efficacy results by the iDMC, who will ultimately provide a recommendation on further dosing.

At least 8 weeks after the second patient is dosed in Cohort 1, the iDMC will review all available safety, tolerability, immunogenicity, and to the extent feasible, efficacy results from the first 2 patients in this cohort (dosed in a staggered manner). At the recommendation of the iDMC, the Sponsor will decide whether to continue dosing the remaining 3 patients in Cohort 1 (low dose) without staggering and in parallel begin staggered enrollment into the mid-dose cohort (Cohort 2). A decision to dose escalate will be based on data from at least 2 patients from the concurrent cohort. However, all cohorts will enroll a minimum of 3 patients, unless enrollment is terminated due to safety concerns or based on biomarker review this dose is considered to be non-efficacious. In all other circumstances, the full cohort of 5 patients will be enrolled.

Cohort 2 will enroll 5 patients to receive the mid-dose ( $7.0 \times 10^{13}$  vg) of PR006A. [REDACTED]  
[REDACTED]. The design for Cohorts 2 [REDACTED] enrollment is the same as for Cohort 1.

If a decision is made to not open or to limit enrollment into a cohort (i.e., Cohort 2 [REDACTED]  

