## **13 Appendices**

### **13.1 Appendix: Schedule of Events**

**Table 13-1 Schedule of Events – Main Study Period**

| Visit Description                                         | Screening/Baseline a,b |                             |                | Treatment      |    |    |    |       |         |                 |   |   |                        | Unscheduled |
|-----------------------------------------------------------|-----------------------------------|-----------------------------|----------------|----------------|----|----|----|-------|---------|-----------------|---|---|------------------------|-------------|
|                                                           | Day                               |                             |                |                |    |    |    | Month |         |                 |   |   |                        |             |
|                                                           | -35 to -2                         | Check-In
-1 c | 0 d | 1 e | 7  | 14 | 21 | 1     | 2       | 3               | 6 | 9 | 12/
ET f |             |
| Visit Window in Days                                      |                                   |                             |                |                | ±1 | ±2 | ±2 | ±7    | +
14 | ±7 g |   |   |                        |             |
| Administrative Procedures                                 |                                   |                             |                |                |    |    |    |       |         |                 |   |   |                        |             |
| Informed consent h                             | X                                 |                             |                |                |    |    |    |       |         |                 |   |   |                        |             |
| Study partner consent i                        | X                                 |                             |                |                |    |    |    |       |         |                 |   |   |                        |             |
| Issue patient identification card                         |                                   | X                           |                |                |    |    |    |       |         |                 |   |   |                        |             |

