| Visit Description                                                                                         | Screening/Baseline a,b |                             |                | Treatment      |    |    |    |    |         |                 |   |   |                        | Unscheduled |  |
|-----------------------------------------------------------------------------------------------------------|-----------------------------------|-----------------------------|----------------|----------------|----|----|----|----|---------|-----------------|---|---|------------------------|-------------|--|
|                                                                                                           | Day                               |                             |                |                |    |    |    |    | Month   |                 |   |   |                        |             |  |
|                                                                                                           | -35 to -2                         | Check-In
-1 c | 0 d | 1 e | 7  | 14 | 21 | 1  | 2       | 3               | 6 | 9 | 12/
ET f |             |  |
| Visit Window in Days                                                                                      |                                   |                             |                |                | ±1 | ±2 | ±2 | ±7 | +
14 | ±7 g |   |   |                        |             |  |
| Blood and urine sample(s) for future biomedical research (optional) w                          | X                                 |                             |                |                |    |    |    |    | X       |                 |   |   | X                      |             |  |
| Lumbar puncture and CSF collection, including optional sample for future biomedical research x | X                                 |                             |                |                |    |    |    |    | X       |                 |   |   | X                      | X           |  |
| Blood sample for biomarkers y                                                                  | X                                 |                             |                |                |    |    |    | X  | X       | X               | X | X | X                      | X           |  |

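### The 8-week minimum gap between patients 1 and 2 of a cohort ends on or before patient 1's Month 2 visit, so it cannot ensure the Month 2 data claimed for it

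*Protocol*

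**What the plan says.** Protocol section 1.2.3 states that "in each cohort, enrollment will be staggered by at least 8 weeks between the first 2 patients". A second gap of at least 8 weeks separates patient 2 from the remaining three. Both gaps are there so that the iDMC can review data and advise on further dosing. Two reasons are given for the length. It covers liver enzyme rises seen at about 3 weeks, and: "It also ensures the iDMC will have appropriate biomarker and safety data from the Month 2 visit to make their recommendation".

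Section 11.1.1 counts the first gap from dose to dose, "such that at least 8 weeks will separate dosing of each patient", and gives its purpose: "This staggering will permit review of safety, tolerability, immunogenicity" and, as far as available, efficacy by the iDMC.

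In Table 13-1, the row "Visit Window in Days" shows ±7 for Month 1 and +14, with no minus side, for Month 2. The row "Lumbar puncture and CSF collection, including optional sample for future biomedical research" is marked at Screening, Month 2, Month 12 and unscheduled visits only.

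For the decision to continue, suspend or escalate, section 1.2.3 adds a separate condition: "Based on the review of data through Month 2 in at least 2 patients and in consultation with the iDMC".

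**The concern.** A minimum waiting time can ensure data from a visit only if the visit and its results must fall inside it. Here the shortest permitted gap and the earliest permitted Month 2 visit meet at Day 56 at best. Nothing in the protocol makes patient 2's dose wait for patient 1's Month 2 visit or its results.

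What can be missed is mainly CSF inflammation without symptoms, which only a lumbar puncture shows. The protocol treats it as something to act on:

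- Section 5.5.1.3 lists "Asymptomatic pleocytosis with WBC" above 30, or high CSF protein, as a reason to consider more immunosuppression.
- Section 6.2.2.4 reports pleocytosis with raised protein in a patient given the sponsor's related AAV9 product, and pleocytosis in another AAV9 trial.
- Section 1.2.3 itself places CSF inflammatory change at 1 to 2.5 months after dosing. Month 2 is the only scheduled CSF sample in that period.

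This is a first-in-human, one-time dose that cannot be withdrawn. The first patient of a cohort is treated alone so that the second can benefit from what was learned.

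**Working it through.** **Inputs**

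- Minimum gap, patient 1 to patient 2: 8 weeks (1.2.3, 11.1.1).
- Minimum gap, patient 2 to the remaining three: 8 weeks (1.2.3).
- Visit windows: Month 1 ±7 days, Month 2 +14 days (Table 13-1).
- First scheduled post-dose lumbar puncture: Month 2 (Table 13-1).
- Cohorts: 3 of 5 patients, 15 in all (7.4).
- Assumption: the protocol gives no day number for a month, so 28, 30 and 30.44 days (365.25/12) are all tried.

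**Formulas**, with m the length of a month in days

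- End of the first gap: 8 × 7 = Day 56.
- Month 2 visit: from 2m to 2m + 14. Distance after the gap ends: 2m − 56 to 2m + 14 − 56.
- Month 1 visit: from m − 7 to m + 7. Time left before Day 56: at least 56 − (m + 7).
- Patient 1's earliest day when the second gap ends: 56 + 56 = Day 112. Margin past the Month 2 window: 112 − (2m + 14).

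| Month length | Month 2 visit (Day) | Days after Day 56 | Month 1 visit (Day) | Least days from Month 1 to Day 56 | Days past Month 2 window at Day 112 |
|---|---|---|---|---|---|
| 28 | 56 to 70 | 0 to 14 | 21 to 35 | 21 | 42 |
| 30 | 60 to 74 | 4 to 18 | 23 to 37 | 19 | 38 |
| 30.44 | 60.9 to 74.9 | 4.9 to 18.9 | 23.4 to 37.4 | 18.6 | 37.1 |

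**Reading the table**

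1. *First gap.* Under every convention patient 1's Month 2 visit comes on or after Day 56. In the single best case the sample is taken on the day patient 2 may be dosed, with no time for a result or a review.
2. *Month 1 checks.* The neurological examination, TNAS and safety MRI at Month 1, and the liver tests from Day 7, all fall inside the gap. The liver rationale for 8 weeks is met.
3. *Second gap.* Patient 1's Month 2 visit is well past. Patient 2 may be only at Day 56, but the condition on data through Month 2 in at least 2 patients covers that decision. That condition cannot operate before patient 2 has been dosed, so the first gap has no counterpart.
4. *CSF period.* 1 to 2.5 months runs to Day 70 (28-day months) or Day 76 (30.44-day months). It is still open when the first gap can end.
5. *Gap needed.* To guarantee only that the visit has happened, the minimum would have to be 70, 74 or 75 days (10.0, 10.6 or 10.7 weeks). With an assumed 7 to 14 days for results and review it would be 11.0 to 12.7 weeks.
6. *Patients exposed.* 1 per cohort × 3 cohorts = 3 of 15 at most.

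**The case against.** The sentence can be read more narrowly. The only iDMC review with stated timing and content is the one at least 8 weeks after patient 2, and that review is protected. The next sentence of 1.2.3 also attaches the CSF reasoning to that later review. On this view the first gap serves the liver rationale and general monitoring, and both are met.

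This does not rescue the text. The 8-week period named in the claim refers back to a sentence that sets both gaps, and 11.1.1 ties the separation of the first two patients to iDMC review in its own right. Even at the later review, it is the separate Month 2 condition that secures patient 2's data, not the 8 weeks.

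Several limits do stand:

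- Eight weeks is a floor. Sites may wait longer, and nothing directs dosing on Day 56.
- The iDMC charter is not shown and may already require a review of patient 1. The protocol does not.
- An unscheduled lumbar puncture is allowed, though not required.
- Asymptomatic pleocytosis in one patient triggers no stopping rule in 4.2.4. The result would inform the decision on patient 2, not bar the dose.
- All patients receive steroids and sirolimus.
- The count of 3 of 15 is an upper limit. Before Cohort 2 opens, Month 2 data from at least 2 patients at half the dose are required. Only patient 2 of Cohort 1 could be dosed with no scheduled post-dose CSF result from anyone.

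It can also be argued that rewording the rationale would be enough. That would correct the text but leave patient 2 without the protection the rationale describes.

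**Conclusion.** The concern holds. For the gap between patients 1 and 2, an 8-week minimum cannot ensure Month 2 data, because patient 1's visit falls 0 to 19 days after the gap may end. The result does not depend on how a month is counted between 28 and 30.44 days, and it assumes no turnaround time, which could only widen the shortfall. The review that governs patients 3 to 5 and escalation is sound.

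The practical exposure is narrow: at most one patient per cohort, only when dosing is near the minimum gap, and mainly to CSF change without symptoms. It is most serious in Cohort 1. The point deserves correction, with medium confidence in its operational effect because the charter may already cover it.

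**What to change.** In the synopsis and sections 1.2.3, 3.1.1 and 11.1.1, state: *In each cohort, patient 2 will be dosed no sooner than 8 weeks after patient 1, and only once the iDMC has reviewed patient 1's Month 2 visit data, including the locally assessed CSF cell count and protein.* The Month 2 window can stay as it is.

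This adds no visits, procedures or patients. In each cohort patient 2 is dosed up to about 14 to 19 days later than the present minimum, plus result turnaround and one short iDMC review of a single patient. Turnaround should be brief, since section 6.8 has CSF cell count and protein read locally. With 3 cohorts that is 3 such reviews, or fewer if the charter already provides for them.
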